## Abstract

**Background:**

Older people usually prefer staying at home rather than going into residential care. The Belgian National Institute for Health and Disability Insurance wishes to invest in home care by financing innovative projects that effectively help older people to stay at home longer. In this study protocol we describe the evaluation of 34 home care projects. These projects are clustered according to the type of their main intervention such as case management, night care, occupational therapy at home and psychological/psychosocial support. The main goal of this study is to identify which types of projects have the most effect in delaying institutionalization of frail older persons.

**Methods/design:**

This is a longitudinal intervention study based on a quasi-experimental design. Researchers use three comparison strategies to evaluate intervention - comparison among different types of projects, comparisons between older persons in the projects and older persons not benefiting from a project but who are still at home and between older persons in the projects and older persons who are already institutionalized. Projects are asked to include clients who are frail and at risk of institutionalization. In the study we use internationally validated instruments such as the interRAI Home Care instrument, the WHO-QOL-8 and the Zarit Burden Interview-12. These instruments are filled out at baseline, at exit from the project and 6 months after baseline. Additionally, caregivers have to do a follow-up every 6 months until exit from the project. Criteria to exit the cohort will be institutionalization longer than 3 months and death. The main analysis in the study consists of the calculation of incidence rates, cumulative incidence rates and hazard rates of definitive institutionalization through survival analyses for each type of project.

**Discussion:**

This research will provide knowledge on the functional status of frail older persons who are still living at home. This is important information to identify determinants of risk for institutionalization. The identification of effective home care projects in delaying institutionalization will be useful to inform and empower home care providers, policy and related decision makers to manage and improve home care services.

## Background

Older people usually prefer staying at home rather than going into residential care [1-3]. Several organizations and professionals provide care for older people at home. In 1994, the World Health Organization defined home care as “an array of health and social support services provided to clients in their own residence. The assumption is that these co-ordinated services may prevent, delay or be a substitute for temporary or long-term institutional care” [4]. A more recent definition of home care defines it as “a phenomenon in which care is provided by professionals to people in their own homes with the ultimate goal of not only contributing to their life quality and functional health status, but also to replace hospital care with care in the home for societal reasons”. In this definition, home care covers a wide range of activities, from preventive visits to end-of-life care [5]. According to the 2009 WHO-report, an appropriate balance between care settings for elderly care is necessary, including supported self-care and home-based service. The report emphasizes the need for interventions to help maintain older people at home and to prevent long-term institutional care [6].

In the literature, several studies about predictors for home care use can be found. The most predominant ones are age, living arrangement, number of informal caregivers, income, medical diagnosis and functional status [1,7]. Moreover, randomized controlled trials have shown that targeted home care can contribute significantly to reduce hospital admission, to delay institutionalization and to improve quality of life [8-10].

In Belgium, 125.000 older people received home care services in 2010 and by 2025 this number will have increased up to 149.000, according to population prognoses [11]. The Belgian National Institute for Health and Disability Insurance (NIHDI)^a^ wishes to invest in home care by financing innovative projects that effectively help older people to stay at home longer. In this study, the effects of these innovative projects are examined as to whether they do keep frail older people longer at home, whether they maintain or improve their quality of life and whether they preserve their autonomy [12-15].

Data from 34 innovative projects will be analyzed. Due to the fact that the projects vary in the scope of the intervention they provide, projects are clustered according to the type of their main intervention such as case management, night care, occupational therapy at home and psychological/psychosocial support. These projects might not be considered to be innovative in other countries. The term ‘innovative’ in the context of this research is defined as interventions which are not yet reimbursed by the Belgian NIHDI. These interventions can be seen as alternatives or add-ons to the standard home care services which are already funded (respite care, nursing care at home, physiotherapy, etc.).

The main goal of this study is to identify which types of projects have the most effect in delaying institutionalization of frail older persons.

## Methods

This is a longitudinal intervention study based on a quasi-experimental design [16]. Due to some constraints, a randomized controlled trial is impossible to realize. The constraints are mostly practical and ethical since all frail older people who wish to benefit from an innovative project cannot be denied access to it. In addition, researchers cannot have total control on the intervention since projects are delivering the services in the ‘real world’. Projects may organize their intervention according to specific types of services. Non randomization and variety of projects impose a thorough description and follow up of beneficiary population and intervention content. The Researchers use three comparison strategies to evaluate intervention – comparison of the arm benefiting from the intervention with older people benefitting from a different type of project, older people who are not benefiting from a project and are still living at home and older people who are already institutionalized.

### Typology of projects

Projects are clustered according to the type of intervention they perform (see Table 1). The typology definition is based on a previous study on the expressed intention and the perspective of actors involved in the project implementation [12].

**Table 1 T1:** Typology of the projects according to main intervention

**Typology**	**Number of projects**
Case-management	8
Occupational therapy	7
Night care	10
Psychological or psychosocial support	9

### Sample size considerations

Beneficiaries will be grouped by type of projects as shown in Table 1 in order to get a reasonable sample size for each side of the comparison. Using an effect size of 0.50, a two-sided significance level of 0.05 and a power of 85%, 75 participants are needed in each group. We expect each project to include at least 45 participants per year because this is the minimum size of case load projects reported at the beginning of their activities. The clusters of projects will have then a larger sample size than indicated by the sample size calculation.

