### Analyses

 – Research question 1 - Do characteristics of populations differ across projects?

In order to answer this first research question comparisons will be made between the populations in the different types of projects to explore whether they present particular characteristics. In these comparisons we will use the variables shown in Table 2 Frequencies will be calculated for categorical variables and means and medians with confidence intervals for continuous variables. Other possible comparison will be done by analysis of variance. All the statistical analysis in the study will be performed with the software Stata 11.1.

 – Research question 2 - Which types of projects are associated with less decline of the functional and cognitive performance of frail older persons?

 – Research question 3 - Which types of projects contribute to a better quality of life of frail older persons?

**Table 2 T2:** Variables to characterize the population of the study

**Topic**	**Variable**	**Source**	**Type of variable**
General information	Civil status	InterRAI HC	Qualitative
	Age	InterRAI HC and IMA	Continuous
	Gender	InterRAI HC and IMA	Dichotomic
Quality of Life	WHOQOL items score	WHOQOL-8	Continuous
Socio-economic status	Financial difficulties	InterRAI HC	Dichotomic
Primary caregiver’s burden	Zarit Burden score	ZBI-12	Continuous
Functional status	Katz score	IMA	Qualitative
	interRAI ADL hierarchy scale	InterRAI HC	Ordinal (0 to 6)
	interRAI IADL scales	InterRAI HC	Ordinal (0 to 48)
	interRAI Communication scale	InterRAI HC	Ordinal (0 to 8)
	interRAI CPS2 scale	InterRAI HC	Ordinal (0 to 6)
	interRAI DRS scale	InterRAI HC	Ordinal (0-14)

Longitudinal analyses will be performed to answer the second and third research questions. Outcome variables will be the interRAI ADL hierarchy scale, the interRAI CPS2 scale and the WHOQOL scale. Mean will be compared between arms of the study and covariate analysis (ANCOVA) will be done to control results for potentially confounding variables.

 The ADL hierarchy scale is a measure of a person’s functional performance. It is based on the concept of early, middle and late loss of ADLs and consists of 4 items from the interRAI instruments: personal hygiene, toilet use, locomotion and eating. The scores vary from 0 to 6 and the higher the score, the greater the dependency [36,37].

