 The cognitive performance scale (CPS2) is an internationally validated scale that describes a person’s cognitive status. The scores vary from 0 to 6 and the scale consists of 5 items from the interRAI HC instrument: skills for daily decision-making, making oneself understood, short-term memory recall, procedural memory and eating impairment. Higher scores indicate a greater degree of cognitive impairment. Several studies have shown a significant correlation between the CPS scale and the Mini-Mental State Examination (MMSE) [38-41].

 – Research question 4 - Which types of projects are associated with a decreased risk of institutionalization of frail older persons?

In order to answer the fourth research question, the definitive institutionalization (more than 90 consecutive days in residential care) will be used as event. The analysis consists of the calculation of incidence rates, cumulative incidence and hazard rates of definitive institutionalization through survival analyses for each type of project. Survival analysis measures the time to a certain event or change of state, in this case, institutionalization. The multivariate Cox model which will be calculated from this analysis will allow us to isolate the effects of the intervention from the effects of confounding variables. These variables are extraneous variables which correlate (positively or negatively) with both the dependent variable and the independent variable. In this analysis we will use the variables of Table 2 as confounding variables. The use of a Cox model may improve the estimate of the intervention effect by narrowing the confidence interval. Another important advantage of this analysis is that it takes into account the variability of covariates across time which makes it very appropriate for longitudinal studies [42-44].

 – Research question 5 - Is the interRAI Maple scale a good predictor of institutionalization in our study?

The fifth research question will be approached by using a multiple logistic regression model with the Methods for Assigning Priority Levels scale (Maple) as one of the independent variables. This interRAI scale is known to be a predictor for institutionalization and can be used as an indicator for allocation of home care resources and prioritization of clients needing community or residential care. MAPLe is an internationally validated predictor of nursing home placements, caregiver distress and ratings that the client would be better off elsewhere [45].

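### Project type is assigned to 34 projects, but the sample size of 75 per group and the named between-type analyses make no allowance for clients being clustered within projects

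*Protocol article*

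**What the plan says.** The Background states: "Data from 34 innovative projects will be analyzed". Table 1, under Typology of projects, assigns each project to one type: 8 case-management, 7 occupational therapy, 10 night care, and 9 psychological or psychosocial support. The stated main goal is to find which types delay institutionalization most.

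Under Sample size considerations: "Using an effect size of 0.50, a two-sided significance level of 0.05 and a power of 85%, 75 participants are needed in each group". Clients are pooled by type: "Beneficiaries will be grouped by type of projects as shown in Table 1 in order to get a reasonable sample size". The expected caseload follows, "We expect each project to include at least 45 participants per year", and the paragraph ends: "The clusters of projects will have then a larger sample size than indicated by the sample size calculation".

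Under Analyses, populations are compared across types descriptively and by analysis of variance. For research questions 2 and 3: "Mean will be compared between arms of the study and covariate analysis (ANCOVA) will be done to control results for potentially confounding variables". For research question 4: "The multivariate Cox model which will be calculated from this analysis will allow us to isolate the effects of the intervention". The adjustment variables are those of Table 2, all measured on the client or the caregiver. Project is not among them.

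**The concern.** All clients of one project share the same exposure, so a comparison of two types is a comparison of two small sets of projects. The article itself gives reasons to expect clients of one project to resemble each other. Projects organise their own services and the researchers do not fully control the intervention (Methods). Caregivers may choose between two frailty scales at intake (Study population). Professional caregivers complete the interRAI, which supplies the ADL and CPS2 outcomes (Data collection). Intake, delivery and rating can therefore all differ between projects.

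If that similarity is ignored, standard errors are too small, and a difference between a few projects can be reported as an effect of a type. Adjusting for client covariates does not put the remaining project-level variation back into the standard error. The result would bear directly on which types the funder sees as effective. The Methods and Discussion acknowledge the lack of randomization, and the Methods also the variety of projects, but neither mentions correlation within projects.

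**Working it through.** **Inputs.** From the article: d = 0.50, two-sided 0.05, power 85%, 75 per group, and at least 45 clients per project per year (Sample size considerations); 8, 7, 10 and 9 projects (Table 1). The article gives no ICC. I assume 0.01, 0.02, 0.05 and 0.10, with equal project sizes.

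**1. Reproducing the 75.** For two independent means, n = 2(1.960 + 1.036)² / 0.50² = 71.8, so 72 per group. The exact t calculation gives 73, and power at 75 is 86.0%. The 75 is therefore an individual-level figure with no room for a design effect.

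**2. True size of a nominal 5% test that ignores project.** Design effect DE = 1 + (m − 1) × ICC with m = 45. True size = 2[1 − Φ(1.96/√DE)].

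| ICC | DE | 1.96/√DE | True size, m = 45 | True size, m = 90 |
|---|---|---|---|---|
| 0.01 | 1.44 | 1.633 | 10% | 15% |
| 0.02 | 1.88 | 1.429 | 15% | 24% |
| 0.05 | 3.20 | 1.096 | 27% | 40% |
| 0.10 | 5.40 | 0.843 | 40% | 53% |

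The last column (two years' caseload) shows that more clients per project makes the error worse.

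**3. Is 75 per type enough for 85% power?** Use a project-level noncentral t test with K₁ + K₂ − 2 degrees of freedom, SE = √[DE(1/n₁ + 1/n₂)] and noncentrality 0.50/SE. Take 7 projects on each side (12 df, critical t = 2.179) as the least favourable case, and let m = n/7. Solving for 85% power gives about 97, 111 and 208 clients per type at ICC 0.01, 0.02 and 0.05. Part of the increase comes from having only 12 degrees of freedom: at ICC 0 the same test needs 86. At ICC 0.10, as clients per project grow without limit, SE tends to √(0.10 × 2/7) = 0.169. The noncentrality is then 2.96 and power levels off at about 77%. With 7 projects per side no number of clients reaches 85%, because the project count is the limit.

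**4. Power at the caseload the article expects.** The smallest real pair is 7 versus 8 projects, with 7 × 45 = 315 and 8 × 45 = 360 clients in one year (13 df, critical t = 2.160).

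| ICC | SE | 0.50/SE | Power |
|---|---|---|---|
| 0.01 | 0.0926 | 5.40 | 99.9% |
| 0.02 | 0.1058 | 4.73 | 99.2% |
| 0.05 | 0.1380 | 3.62 | 91.7% |
| 0.10 | 0.1793 | 2.79 | 73.2% |

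Power falls below 85% at an ICC of about 0.068. For 9 versus 10 projects the crossing is at about 0.097. If questionnaires cover only the required 75% of clients (0.75 × 45, about 34 per project), the 7 versus 8 crossing moves to about 0.061.

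**The case against.** **The study still has its power.** This stands. A reader might infer that the study is underpowered, but the article expects 315 to 450 clients per type in a year. At that caseload even the smallest pair exceeds 85% power at ICC 0.05. The claim that each type will exceed the required size also survives correction there: 315 against about 208.

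**Simple corrections overstate the problem.** This stands too. Multiplying 73 by the design effect at m = 45 gives 137, 234 and 394 per type at ICC 0.02, 0.05 and 0.10. Those figures imply about 3.0, 5.2 and 8.8 projects per type, not the 7 to 10 of Table 1. The last one wrongly suggests that a client target would be enough at ICC 0.10 with 7 projects. Likewise, power for 75 clients spread over 7 projects describes a study nobody plans.

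**The analysis part argues from silence.** This stands in part. The article condenses a fuller protocol, never says that clients are treated as independent, and naming a Cox model does not exclude a frailty term or clustered standard errors. But the sample size paragraph is fixed on the page, and it draws its conclusion by comparing pooled client counts with an unclustered requirement. The named models and their covariate list, followed as written, give the error rates above.

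**The magnitudes are assumed.** The ICCs are not from the article, and the design effect applies to an unadjusted comparison of means. It is only an approximate guide for the Cox analysis, which serves the main goal.

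**Conclusion.** The point holds, chiefly as a problem of false-positive error. The exposure varies between projects, while the sample size and the analyses as named work on clients. Even an ICC of 0.01 about doubles the nominal 5% error at 45 clients per project, and large pooled counts are no defence. The threshold of 75 is not sufficient for 85% power once projects are the unit, although the planned numbers are well above it. Whether power is adequate depends on the ICC: yes for all pairs up to about 0.07 at one year's expected caseload, and no for the smallest pair at 0.10. These results assume equal project sizes, no dropout, d = 0.50 and a comparison of means.

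**What to change.** - **Research questions 2 and 3:** use a linear mixed model with a random project effect, a client effect for repeated measures, and the baseline value as covariate. Base the degrees of freedom on the number of projects (34 projects less 4 types, about 30) rather than on clients.
- **Research question 4:** use a Cox model with project-level shared frailty. Project-clustered standard errors are an alternative, but with 7 to 10 projects per type they are themselves anti-conservative, and the text should say so.
- **Research question 1:** where types are compared by a test, account for project there as well.
- **Sample size considerations:** replace the closing sentence with power for each pair of types, computed from the number of projects and clients per project over a stated ICC range such as 0.01 to 0.10.

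The cost is wider confidence intervals and a less favourable stated power. No extra clients are needed. Whether the named software, Stata 11.1, provides the small-sample correction should be checked before the method is fixed.

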### Study population

The study will include older people receiving home care services who are at least 65 years old. Projects are asked to include only clients who are frail and at risk of institutionalization. Due to practical reasons, frailty is measured in the study with two different scales and caregivers are allowed to choose between them. One of these scales is the Edmonton Frail Scale [17,18] with a cutoff point of 6. Another scale is an adapted version of the Katz scale for Belgian home care and residential care [19]. Older people with a Katz score equal to A, B or C will be included [20]. Clients who have been diagnosed with dementia by a geriatrician, neurologist or psychiatrist may also be included in the study.

Each project has to collect data on at least 75% of their total client population in order to ensure representativeness. This means that caregivers have to complete questionnaires for at least 75% of clients benefiting from their projects.

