### Ethical approval and informed consent

This observational study was approved by the Belgian Privacy Commission and by the Ethics committee of the Belgian Universities - Université Catholique de Louvain and Katholieke Universiteit Leuven with dossier number B40320108337. A formal procedure was implemented so that caregivers could fill out the questionnaires on a secured website.

For this study, older persons are asked to sign an informed consent agreement. In case they are not capable of signing this document, a family member or another legal representative will sign it on their behalf, as stipulated by Belgian law [21]. Clients do not undergo the intervention because of the research. The research however evaluates the effects of the intervention. Clients have the right not to participate in the research and they may withdraw their consent at any time. In that case, all data for this person is removed. Their consent or refusal to consent does not affect their participation in the intervention.

All data are anonymized and analyzed according to the rules of the Belgian Privacy Commission [22].

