### Data collection

Professional caregivers are asked to fill out the interRAI Home Care instrument. Clients fill out the WHO-QOL-8 and the main informal caregivers complete the ZBI-12. These questionnaires are filled out at inclusion of the frail older person in the project (baseline), at exit from the project and 6 months after baseline. Additionally, if clients stay longer than 6 months in the project, caregivers have to do a follow-up every 6 months until the moment clients leave the project. Follow-up of clients happens from March 2011 until July 2013. A client follow-up period will vary between 6 to 36 months. Criteria to exit the cohort will be institutionalization longer than 3 months and death. Follow up will also end for clients who leave the projects.

Professional caregivers are instructed on how to fill out the questionnaires during a 2-day training and a follow up training of 1 day. They fill out the interRAI HC based on observation and on interview of the older person and of the main informal caregiver.

The interRAI-data will be linked with data from the national database IMA (Inter-mutuality Agency). This database contains data on national health service consumption reimbursed by NIHDI such as medication use, hospital days, medical, nursing and physical therapy use, etc. This data will be added to the analysis for the clients in the projects.

The “permanent sample” of people over 65 extracted from IMA database will also serve as a control group for our study population. By using this database we will be able to compare older persons who are benefiting from the innovative projects with older persons who are not benefiting from these projects (control group). In this control group we will have two major groups – clients who are still living at home and clients who are institutionalized. All clients who are in the projects and have not given their informed consent will be excluded from this database.

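### A 75% coverage minimum limits how many clients are missing, not which ones, so it does not ensure representativeness

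*Protocol article*

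**What the plan says.** Under Study population, the protocol article sets a coverage rule and gives its purpose: "Each project has to collect data on at least 75% of their total client population in order to ensure representativeness". The next sentence makes it operational: "This means that caregivers have to complete questionnaires for at least 75% of clients benefiting from their projects". The denominator is all clients of a project. No rule, such as consecutive or random inclusion, says which clients must be among the 75%.

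Under Data collection, the main instrument is completed by project staff: "Professional caregivers are asked to fill out the interRAI Home Care instrument". Baseline assessment takes place at inclusion in the project. The interRAI data are then linked to the IMA claims database.

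Under Ethical approval and informed consent, clients may decline: "Clients have the right not to participate in the research and they may withdraw their consent at any time". On withdrawal, the person's data are removed. Data collection adds, about the IMA control sample: "All clients who are in the projects and have not given their informed consent will be excluded from this database".

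The Background says that the funder "wishes to invest in home care by financing innovative projects that effectively help older people to stay at home longer". The stated main goal is to find which project types do most to delay institutionalization.

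**The concern.** A coverage quota controls the amount of missing data, whereas representativeness depends on the pattern. A project can meet the 75% while the clients without data are those who left soon after entry, were hard to assess, or refused consent for reasons linked to their prognosis. The article nevertheless presents the quota as securing representativeness.

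What is at stake is the main comparison. Research question 4 contrasts incidence and hazard of definitive institutionalization between four project types. Selective omission that differed between types would enter that contrast directly. A larger sample would not help, because the bias does not shrink with the number of clients.

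**Working it through.** **Inputs**
- Omitted fraction f: up to 1 − 0.75 = 0.25 per project (Study population).
- Rule on which clients may be omitted: none stated.
- Risk ratio r of omitted to included clients: not given; assumed 0.5 to 3.
- True institutionalization risk: not given; it drops out of the ratio below, and 20% is used only as an example.

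**The plan's own figures.** The 75% coverage is a rule without a derivation, so there is nothing to reproduce. The only computed figure is the sample size: "Using an effect size of 0.50, a two-sided significance level of 0.05 and a power of 85%, 75 participants are needed in each group". A two-sample t-test calculation gives 72.8, so 73 per group (72 by the normal approximation), and 75 per group gives 86.0% power. That figure is sound, but it concerns precision and has no bearing on who is missing.

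**Effect on one type's risk.** Let q be the risk among included clients and r·q the risk among omitted clients. Then

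true risk = (1 − f)·q + f·r·q, so observed/true = 1 / (1 − f + f·r).

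With f = 0.25:

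| Assumed r | 0.75 + 0.25·r | Observed/true | A true 20% appears as |
|---|---|---|---|
| 0.5 | 0.875 | 1.14 | 22.9% |
| 1 | 1.000 | 1.00 | 20.0% |
| 1.5 | 1.125 | 0.89 | 17.8% |
| 2 | 1.250 | 0.80 | 16.0% |
| 3 | 1.500 | 0.67 | 13.3% |

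**Effect on the comparison of two equally effective types (crude risk ratio).** Divide one type's factor by the other's:
- 25% omitted at r = 2 against no omission: 0.80 / 1.00 = 0.80.
- 25% omitted at r = 0.5 against no omission: 1.14 / 1.00 = 1.14.
- 10% omitted at r = 2 against no omission: 1 / (0.90 + 0.20) = 0.91.
- The same f and the same r in both types: 1.00.

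These are unadjusted risks. The planned analysis is a Cox model, so the figures show scale and do not predict the hazard ratio.

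**Does another section cover the gap?**
- Research question 1 compares included populations between project types, not included with omitted clients.
- The IMA linkage is described for the interRAI data, so as written a client without an interRAI record is not recovered through claims.
- The Cox model adjusts for the Table 2 variables. This handles omission that depends only on those variables, but not omission that depends on unmeasured prognosis or on events after entry.
- The limitations in the Discussion name lack of randomization and variables missing in the control group, not selective coverage.

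**The case against.** Several stronger readings are tempting, and the article does not support them.

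- **That caregivers choose whom to leave out because they have an interest in the result.** No section says so. The article says who completes the forms and that the funder wants to finance effective projects. Choice and motive are inferences. The point needs neither, since early exits and hard assessments can be missed without intent.
- **That refusal of consent explains only part of the 25%.** No refusal rate is given. The denominator is all clients, while projects are asked to include only frail, at-risk people aged at least 65. Refusal, withdrawal and ineligibility could fill the whole gap. Refusal need not be random, however, so representativeness would still not be secured.
- **That institutionalization is understated.** The direction is unknown: the same formula gives 1.14 at a risk ratio of 0.5.
- **That adjustment cannot repair the bias.** It can, where omission depends on measured baseline variables. Difficulty of assessment, for instance, is likely to relate to the CPS2 and Communication scales, both in Table 2.

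Baseline assessment at inclusion also places most decisions before the client's course is known, which narrows the problem. It does not close it, because the quota is not tied to a list made at entry, and a client who leaves before assessment can fall within the permitted 25%.

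Finally, an article may leave recruitment instructions to the full protocol or to staff training. That is fair for the missing log, but not for the printed claim about what the quota achieves.

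**Conclusion.** The point holds in this limited form: the 75% minimum bounds non-coverage and does not, by itself, ensure representativeness. Selective omission biases the comparison between types only if it differs between types and depends on factors that the Table 2 adjustment does not capture. Neither condition can be confirmed or excluded from the article.

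Under the assumed risk ratios of 0.5 to 3 with the full 25% omitted, a type's observed risk lies between 1.14 and 0.67 of its true risk. The larger between-type distortions also require the two types to use the allowance very differently. Random omission, or equal omission in both types, leaves the risk ratio unbiased. The size and sign of any real bias are unknown, but the main comparison is exposed and the remedy is cheap, so the change should be made.

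**What to change.** 1. List every eligible new client consecutively at project entry, before the course is known. Seek consent and baseline data for all of them, and treat 75% as a minimum completion rate on that list.
2. Keep counts of omitted clients by project type and reason. For clients who refuse or withdraw consent, keep anonymous counts only, in line with the consent section and the exclusion of non-consenting clients from the IMA data.
3. For research question 4 only, add a sensitivity analysis that includes consenting clients without questionnaires through IMA linkage. Adjust for the Table 2 covariates that IMA holds: age, gender and Katz score. With so few covariates, confounding is less well controlled, so this analysis supports the planned Cox model and does not replace it.
4. Replace the representativeness claim with wording that the minimum limits non-coverage.

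The cost is a short entry list per project and one extra sensitivity analysis. No additional client assessments are needed beyond the baseline data already planned.
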